### Ethics Approval, Study Registration, and Consent to Participate

The study will be conducted in accordance with the tenets of the Declaration of Helsinki. Ethical approval was obtained from the ethics committee of the Deutsche Hochschule für Gesundheit und Sport (DHGS-EK-2021-001), and the study was registered with the German Clinical Trials Register (DRKS00023881) and in the World Health Organization’s International Clinical Trials Registry Platform (U1111-1262-6569). Participants will be required to sign the informed consent form and return it during recruitment to the same physiotherapist who informs them of their study group allocation.

### Protocol Amendments

Any major amendment to the study protocol will be communicated to the responsible ethics committee and the trial registration body.

### Safety and Data Monitoring

Participants are insured by the existing insurance policy at Reha Center Michaeliskarree. During the trial, participants will be continuously monitored for possible occurrence of any side effects of the treatments. Most side effects as reported from previous studies, and as observed by the investigators, are minor and disappear shortly afterward. In the event of an established more serious side effect, the patient will be immediately referred to the hospital. All documented side effects will be reported in a separate publication. The lead investigator and research team will monitor the safety and scientific integrity of the trial.

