Stochastic resonance therapy (SRT) is a form of whole-body vibration therapy that uses randomized stimuli that are amplified with the help of noise [27]. The vibration output from SRT is different from that of a regular WBV in that it is random and unpredictable. Thus, the patient is constantly challenged to adapt to the multidimensional perturbations from the device’s standing platform [28,29]. Previous studies have suggested potential therapeutic benefits of the SRT [28,30-32]. For example, Kaut et al [31] reported increased postural stability in patients with Parkinson disease after administration of SRT. SRT is also known to reduce musculoskeletal pains [32,33]. Furthermore, a recent systematic review and meta-analysis indicated improvements in postural control and balance performance in healthy young adults, older adults, and people with lower extremity injuries after stochastic stimulation [34].

Until now, the effects of SRT and WBV in cervical pain are not known. Thus, this study aims to answer the research question which treatment among BLT, WBV, and SRT has the greatest effect in reducing pain intensity, the pressure pain threshold (PPT), and neck disability and in improving CJPS acuity in patients with chronic neck pain.

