### Study Setting and Participants

The study will be conducted at the Reha Center Michaeliskarree GmbH (an outpatient rehabilitation center) in Hof, Bavaria, Germany. Participants will be recruited through advertisement posters placed at the rehabilitation center and other health facilities in the neighborhood. We will recruit a total of 45 participants for the study, who are allocated to 3 arms of 15 participants per group: SRT, WBV, and BLT. We plan to recruit 2 additional patients per group to be sure that our design will not be underpowered in case of an approximately 15% dropout.

The progression of the trial is summarized in Figure 1. Participants will be included in the study if they have grade 1 neck pain without daily interference and grade 2 neck pain, which interferes with daily activities [36] for 3 months or longer, are between the ages of 18 and 65 years, and sign a written informed consent form. The following exclusion criteria are applied: the presence of potential contraindications to vibrations (eg, pregnancy and fresh medical procedures), uncontrolled high blood pressure or low blood pressure, kidney stones, glaucoma, acute thrombosis, advanced osteoporosis, presence of neurological conditions, epilepsy, rheumatoid arthritis, acute hernia, schizophrenia, pacemaker, aneurysm, heart arrhythmias and tumors or metastases, and uncontrolled diabetes. Furthermore, patients with the following pre-existing conditions shall be excluded: vertigo, dizziness, diabetic disorders, vertebrobasilar insufficiency, limiting pain, difficulties understanding instructions, difficulties adopting the required posture on the devices, whiplash-associated disorder, and traumatic injury to the neck.

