### Outcome Measures

#### Overview

Pre- and postintervention measurements and outcome data shall be assessed by [name]. [name] is a sport scientist with a cumulative work experience of 6 years as a physical education teacher and sports therapist. [name] is trained in using the underlisted assessment instruments and procedures.

Pain intensity, PPT, neck disability, and CJPS are measured before, immediately after, and 15 minutes after the first intervention session and after 4 weeks of the intervention. A follow-up postintervention measurement will be taken after 4 weeks.

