### Statistical Analysis

Statistical analyses will be performed using SPSS (version 24; SPSS Inc). Descriptive statistics will be used to report the study population’s demography and characteristics. The Gaussian distribution of data will be assessed using the Shapiro-Wilk test. Thereafter, mixed ANOVA will be used to determine the main and interaction effects of within (before intervention, after intervention 1, after intervention 2, after intervention 3, and follow-up) and between (SRT, WBV, and BLT) factors on the study outcome variables. Mean (SD) values, effect sizes, and 95% CIs are reported.

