### Dissemination Policy

The results will be communicated to the participants and shared publicly through publication in peer-reviewed journals and at international scientific conferences.

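### All side effects are assigned to a separate publication, so the paper comparing SRT, WBV and BLT is not planned to show harms by arm

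*Protocol article*

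**What the plan says.** The Safety and Data Monitoring section commits to collecting harms: "participants will be continuously monitored for possible occurrence of any side effects of the treatments". It says that most side effects seen so far were minor and short-lived, and that a patient with an established more serious one will be sent to hospital. It then fixes where harms will be reported: "All documented side effects will be reported in a separate publication".

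The Introduction sets a comparative aim, namely "which treatment among BLT, WBV, and SRT has the greatest effect in reducing pain intensity" and the other outcomes. Under Outcome Measures, the Overview names four outcomes, all of them efficacy measures: "Pain intensity, PPT, neck disability, and CJPS are measured before, immediately after, and 15 minutes after the first intervention session", with later measurements after the 4-week programme and at follow-up. The Statistical Analysis section applies a mixed ANOVA to the outcome variables and adds that "Mean (SD) values, effect sizes, and 95% CIs are reported". The Dissemination Policy says that results will be "shared publicly through publication in peer-reviewed journals and at international scientific conferences".

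**The concern.** The sentence on side effects is a stated choice, so it cannot be excused as detail that a condensed article leaves to a fuller document. It says all side effects, and it says a separate publication. If that is carried out as written, readers of the comparative results see which arm did best on pain, pressure pain threshold, disability and joint position sense, but not what each arm cost in side effects.

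That matters in this trial for three reasons.

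- Two arms receive vibration and one does not, so the arms may differ in tolerability. The Study Setting and Participants section excludes patients with a long list of potential contraindications to vibration, and the Limitations section explains that this was done to avoid exposing such patients to risk.
- Under Expected Findings the authors say that, to their knowledge, this is the first study of SRT and WBV in this population. By their own account, a reader cannot turn to an earlier trial in these patients to fill the gap.
- Harms held for a second paper depend on that paper being written. Reporting them with the comparison lowers the risk of selective or delayed harms reporting.

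**Working it through.** The plan gives no figure on this point, and no sample size, power or error rate enters it. The check sets side by side every section in which harms could have been placed with the efficacy results.

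1. **Safety and Data Monitoring.** Side effects are monitored and documented. All of them are assigned to a separate publication. No by-arm summary is mentioned.
2. **Outcome Measures, Overview.** There are four outcomes: pain intensity, pressure pain threshold, neck disability and cervical joint position sense. None is a harms outcome.
3. **Statistical Analysis.** The mixed ANOVA and the reported summaries concern the study outcome variables, which are the four in step 2. Side effects are not mentioned.
4. **Dissemination Policy.** Publication of the results is promised in general terms. Nothing says that harms and efficacy will appear together.
5. **Introduction, research question.** The purpose is to find which of the three treatments has the greatest effect. The results paper will therefore compare the arms on the outcomes in step 2.

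Steps 2 to 4 contain nothing that brings side effects back beside the comparison in step 5. With step 1 sending all of them elsewhere, the natural reading is that the comparative paper is not planned to carry them.

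The next question is what the trial will have in hand for a by-arm table.

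- Documented side effects will exist, because the section says they are documented.
- Referral to hospital is named as the response to a more serious side effect, so those cases should be identifiable. The article gives no definition or grading of seriousness.
- The article does not say that reasons for discontinuing will be recorded. A count of participants who stopped because of a side effect is available only if they are.

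The design is "3 arms of 15 participants per group: SRT, WBV, and BLT", so such a table would be short. The Results section reports 20 patients enrolled as of May 2022, with analysis to begin only after completion. On those dates there was time to settle the reporting plan before any results were analysed.

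**The case against.** The strongest reply is that the sentence does not say what the publication is separate from. It stands in a protocol article, so it could mean only that side effects are not reported in this article, which would leave the results paper free to include them. That reading is possible but strained: a protocol without outcome data would not report side effects anyway, so the sentence would say nothing. What stands is that the absence of harms from the comparative paper is an inference. The document never speaks of a main paper and does not forbid a short harms summary there.

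It can also be said that harms are to be monitored, documented and published, that most are described as minor, and that the exclusion criteria were chosen to reduce risk. All of this is in the text. It shows that nothing is being hidden and it limits the seriousness of the point, but it does not bring the harms beside the comparison they qualify.

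Two stronger readings are tempting and not supported.

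- A reader might infer that withdrawals due to side effects would go unseen. The sentence covers documented side effects only. Nothing says that withdrawals or their reasons will be held back, and the study flowchart is not available in the text reviewed.
- A reader might try to size the problem by computing how high a true event rate could be when none is seen among 15 patients. That limit follows from the arm size and is the same whichever paper reports the events. It describes imprecision, not the effect of separating the publications.

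**Conclusion.** The concern holds as a point about reporting. The plan assigns all documented side effects to a separate publication, and no section places them with the efficacy comparison. On its natural reading, the paper comparing SRT, WBV and BLT is not planned to show side effects by arm. The fault is the separation, not suppression.

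It has no effect on power or type I error and no numerical size. It deserves a change because the change is specific and cheap and lets readers judge benefit and harm together. The conclusion rests on two assumptions: that separate means separate from the efficacy results, and that no fuller document, not shown here, already provides for harms in the comparative paper. If either is wrong, the sentence still needs rewording to say so.

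**What to change.** In Safety and Data Monitoring, replace the sentence on separate publication with wording such as:

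> The paper reporting the efficacy comparison will also give, for each arm, the number of participants with any documented side effect, the number with a more serious side effect (including any hospital referral) and, where recorded, the number who discontinued because of a side effect. A more detailed separate publication may follow.

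The cost is one extra table and less new material for the second paper. The first count uses data the trial already plans to document. The second needs a consistent record of which events were treated as more serious. The third requires reasons for discontinuation to be recorded, which the article does not currently state. No change to treatment, follow-up or the efficacy analysis is needed.

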## Results

Recruitment of participants started in May 2021. In total, 20 patients have been enrolled as of May 2022. All participants are expected to have completed the trial by the end of 2022, and analysis of data will commence thereafter.

## Discussion

### Expected Findings

We hypothesize that all 3 interventions will reduce neck pain and improve the sensorimotor function of the cervical spine. Furthermore, we hypothesize that SRT elicits larger effects than WBV owing to the random and multidimensional nature of the former, thus being a more challenging application of the vibration stimuli. Finally, we hypothesize that BLT elicits the most beneficial effects as it incorporates the coordinatively most challenging tasks and is known to upregulate the inhibitory GABAergic system in the brain, which is also needed to suppress the perception of pain.

Manufacturers of vibration devices have touted their benefits for muscle activation, bone strengthening, and treatment of several health conditions. Indeed, some of these claims are supported by research, as suggested by the latest up-to-date reviews of the literature and meta-analysis [43,44]. However, to the best of our knowledge, this would be the first study to investigate the treatment effects of SRT and WBV in patients with chronic nonspecific neck pain and to compare these effects with BLT. The results from this study will contribute to our understanding of the role of WBV (stochastic and nonstochastic) and BLT in the management of chronic neck pain. It is hoped that this study spurs further research in the application of SRT, WBV, and BLT as treatment options for neck pain. Future studies should further explore how the human neck region responds to WBV stimuli and if this response is correlated with pain reduction and sensorimotor function improvement.

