### Interventions

All 3 groups will train 3 times per week for 4 weeks. The SRT group will train on an SRT device (SRT Zeptor Medical-plus noise, Zeptoring), while the WBV group will train on Galileo Sport (Novotec Medical). The BLT group will perform balance exercises on different unstable devices. All participants will be instructed not to seek any other neck-specific therapy except in case of an emergency, and such events should be documented and reported to the researchers.

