### Conclusions

The outcome of this study will particularly elucidate the effects of SRT, WBV, and BLT on pain and function in patients with chronic neck pain.

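### The hypothesis that all three interventions reduce pain and improve function cannot be tested without an untreated or sham arm, and a significant time effect could be mistaken for efficacy

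*Protocol article*

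**What the plan says.** Under Study Setting and Participants, patients are "allocated to 3 arms of 15 participants per group: SRT, WBV, and BLT". Under Interventions, "All 3 groups will train 3 times per week for 4 weeks". No arm is untreated, wait-listed or given a sham.

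Under Expected Findings there are three hypotheses. The first is absolute: "We hypothesize that all 3 interventions will reduce neck pain and improve the sensorimotor function of the cervical spine". The other two are comparative: SRT does better than WBV, and BLT does best. The research question at the end of the Introduction is also comparative, asking which of the three has the greatest effect.

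Under Statistical Analysis, "mixed ANOVA will be used to determine the main and interaction effects", with five measurement occasions as the within factor and a "between (SRT, WBV, and BLT) factors on the study outcome variables". Under Outcome Measures, Overview, the outcomes are "measured before, immediately after, and 15 minutes after the first intervention session and after 4 weeks of the intervention", with a follow-up after that.

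Limitations names two matters: the strict exclusion criteria and the assessor who could not be blinded. It does not mention the absence of an untreated or sham comparator.

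**The concern.** The first hypothesis says that each treatment works. To test it, the trial would need to know what these patients would have done without treatment, and no arm supplies that. The group effect and the group-by-time interaction compare active treatments with one another. If all three arms improve equally, these tests cannot separate three effective treatments from three ineffective ones.

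That leaves the time effect, which contains everything that changes between baseline and later visits. The document itself leaves room for several sources of change other than treatment:

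- Volunteers recruited by poster may come forward when their pain is worse than average (regression to the mean and natural fluctuation).
- Pain and disability are self-reported, with no sham to control expectation.
- The joint position test is done 8 times per side on each of five occasions.
- The assessor is unblinded and applies the algometer pressure by hand.

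Nor can an established reference treatment stand in for the missing comparator. The Introduction says the effects of SRT and WBV in cervical pain are unknown, and it cites one first exploration of BLT in neck pain. At stake is whether an improvement in all arms would be reported as benefit from all three treatments.

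**Working it through.** **Which planned effect answers which hypothesis**

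| Hypothesis (Expected Findings) | Planned effect that bears on it | Protected by randomisation? |
|---|---|---|
| All three reduce pain and improve function | Change over time | No |
| SRT better than WBV | Group-by-time contrast | Yes |
| BLT best | Group-by-time contrasts | Yes |

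The plan gives no figure for change expected without treatment, so there is nothing of its own to reproduce. The sample size was set for the interaction and does not enter this point. The size of the problem can only be illustrated under assumptions.

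**Illustration 1: regression to the mean, pre-post test**

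Inputs:
- n = 45 in total, 15 per arm (Study Setting and Participants).
- r = .67 (Pain Intensity). The article calls this reliability but does not say it is a test-retest correlation, so using it as one is an assumption.
- k = 0.5, 0.75 or 1: how many SDs the group's observed baseline mean lies above the mean of its source population. Assumed; the eligibility criteria set no minimum pain score.
- No treatment effect, two-sided α = .05, and the same SD at both occasions.

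Formulas:
- Expected fall = (1 − r)k = 0.33k SD: 0.165, 0.248, 0.330.
- SD of the difference = √(2(1 − r)) = √0.66 = 0.812.
- Noncentrality = fall / 0.812 × √n, referred to the noncentral t with n − 1 degrees of freedom.

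| k | Noncentrality, n = 45 | P(significant), n = 45 | Noncentrality, n = 15 | P(significant), one arm of 15 |
|---|---|---|---|---|
| 0.5 | 1.36 | 27% | 0.79 | 11% |
| 0.75 | 2.04 | 52% | 1.18 | 20% |
| 1 | 2.72 | 76% | 1.57 | 31% |

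Because the meaning of .67 is uncertain, r was varied for the pooled test. For k = 0.5, 0.75 and 1, r = .8 gives 18%, 34% and 55%; r = .5 gives 37%, 69% and 91%.

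**Illustration 2: the planned mixed ANOVA**

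The five-occasion analysis was simulated with 3 × 15 patients, an assumed correlation of .5 between occasions, no treatment effect in any arm, and a common non-specific improvement at the last two occasions (4,000 runs per setting).

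| Common shift (SD) | Time effect significant |
|---|---|
| 0 | 5% |
| 0.2 | 35% |
| 0.3 | 69% |
| 0.4 | 92% |
| 0.5 | 99% |

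The interaction test stayed between 4.8% and 5.5% throughout. A shift shared by all arms therefore inflates the time effect and leaves the randomised comparison intact.

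**The case against.** The strongest reply is that the trial is comparative in its question, its sample size calculation and two of its three hypotheses. A mixed ANOVA always produces a time term, and reporting it is not a claim of efficacy. The absolute hypothesis stands in the Discussion as an expectation, not as a decision rule. Most of this is right, and it limits the point to the first hypothesis. It does not remove it: the hypothesis is stated, and no planned effect other than change over time can address it.

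Some of the mechanisms are possibilities rather than demonstrated facts. Pain lasting 3 months or longer makes spontaneous recovery less likely. The joint position test is done blindfolded with no feedback described, so practice gains are not certain. The article does not say that poster recruits come at a symptomatic peak. Grade 1 pain without daily interference is admitted, so the values of k have no support in the document. This stands against the size of the effect, not against its direction.

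Three stronger readings are tempting and are not supported:

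- *The protocol will take a time effect as proof of efficacy.* No sentence says so.
- *The trial is likely to declare all three treatments effective when none is.* The 27% to 76% belongs to one pooled test, which cannot show that each arm improved. If each arm of 15 had to be significant on its own, the chance that all three are is the single-arm figure cubed: about 0.15%, 0.8% and 3.0% for k = 0.5, 0.75 and 1.
- *The closing statements overclaim.* The Conclusions section says "The outcome of this study will particularly elucidate the effects of SRT, WBV, and BLT on pain and function", which promises information and asserts no benefit.

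**Conclusion.** The point holds for the first hypothesis only. It is an absolute claim that three active arms and a mixed ANOVA cannot test, and a significant time effect could be mistaken for efficacy. That rests on the stated arms, hypothesis and analysis alone.

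The size is illustrative. The ranges in the first table depend on reading .67 as a correlation between occasions and on assumed values of k. Here k describes a group mean relative to its source population. It does not describe patients relative to their own usual level; a group k SD above its own usual level would be expected to fall by the full k SD. Every combination tried exceeds the nominal 5%.

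The question in the Introduction and the SRT-versus-WBV and BLT-best hypotheses are randomised comparisons and are unaffected. The change is worth making because it settles what the trial may conclude if all arms improve together.

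**What to change.** Three changes of wording:

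1. **Expected Findings:** restate the first hypothesis as a description of within-arm change, reported as mean change with 95% CI for each arm and with no claim of efficacy.
2. **Statistical Analysis:** state that the main effect of time is not evidence of treatment efficacy and that treatment conclusions rest on the group-by-time (between-arm) contrasts.
3. **Limitations:** add that there is no untreated or sham comparator, so improvement common to all arms cannot be attributed to treatment.

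Conclusions needs no change. No new arm, patient or visit is required. According to Results, data analysis had not begun, so the change can precede it. The cost is giving up a claim that the design cannot support.
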